# SCHISTOACT: a protocol for an open-label, five-arm, non-inferiority, individually randomized controlled trial of the efficacy and safety of praziquantel plus artemisinin-based combinations in the treatment of *Schistosoma mansoni* infection

**DOI:** 10.1186/s13063-023-07790-3

**Published:** 2023-11-27

**Keywords:** Schistosomiasis, Artemisinin, Praziquantel, Combinations, Children, Randomized controlled trial

## Abstract

**Background:**

Schistosomiasis control relies on praziquantel for preventive chemotherapy. Alternative drugs are needed for the treatment and control of schistosomiasis. Praziquantel is effective against adult schistosome worms but ineffective against larval stages of the parasite and cannot prevent re-infection or interrupt the transmission of infection. Continued reliance on praziquantel for wide-scale schistosomiasis control will likely accelerate the emergence of drug resistance. Artemisinin derivatives are effective against the juvenile stages but ineffective against adult worms. The SCHISTOACT study aimed to evaluate the efficacy and safety of praziquantel plus one of four artemisinin-based combinations in treating *Schistosoma mansoni* infection in Kenya.

**Methods:**

The SCHISTOACT study is an open-label, head-to-head, five-arm, proof-of-concept, non-inferiority, individually randomized controlled trial with a follow-up of 12 weeks. A total of 540 primary school-aged children from the Mwea area, Kirinyaga County in central Kenya, diagnosed with *S. mansoni* infection (by Kato-Katz method) are randomly allocated (1:1:1:1:1) to a single dose of praziquantel plus a 3-day course of artesunate-sulfalene/pyrimethamine, or artesunate-amodiaquine, or artesunate plus mefloquine, or dihydroartemisinin-piperaquine, or praziquantel control arm. The primary endpoints are efficacy (cure rate, assessed by microscopy) and safety (adverse events) of each study arm 6 weeks after treatment. Secondary endpoints include cumulative cure rate, egg reduction rate, and re-infection 12 weeks after treatment. The non-inferiority margin is set at − 10 for the risk difference in cure rates between praziquantel and the combined treatment.

**Discussion:**

This study assesses a strategy for repurposing artemisinin-based combination therapies (ACTs) for treating schistosomiasis. It adopts a head-to-head comparison of four different ACTs to test a non-inferiority hypothesis and to strengthen local capacity to conduct clinical trials for interventions against neglected tropical diseases.

**Trial registration:**

Pan-African Clinical Trials Registry PACTR202001919442161. Retrospectively registered on 6 January 2020

**Supplementary Information:**

The online version contains supplementary material available at 10.1186/s13063-023-07790-3.

## Introduction

Human schistosomiasis is an important but neglected debilitating water-borne parasitic disease caused by trematode worms of the genus *Schistosoma*. The three most common schistosome species that infect man include *Schistosoma mansoni*, *S. haematobium*, and *S. japonicum* [1]. Human schistosomiasis presents clinically as an intestinal or urogenital form. The global burden of schistosomiasis is estimated at 1.4 to 3.3 million disability-adjusted life years annually [2]. Over 90% of the 250 million people infected with schistosomiasis reside in sub-Saharan Africa, where *S. mansoni* and *S. haematobium* are the most prevalent [3]. The high-risk groups for schistosomiasis include preschool-aged and school-aged children and adults with occupations that involve contact with infested water, such as fishermen, car washers, irrigation workers, farmers, and women doing domestic chores [4].

The global schistosomiasis control strategy recommended by the World Health Organization (WHO) is based on preventive chemotherapy [5]. Praziquantel is currently the only drug available for preventive chemotherapy; it is effective against all the species of human schistosomiasis; it can be administered as a single oral dose, is affordable, safe, and partially effective [6]. Praziquantel is effective against the invasive stages and adult schistosome worms but less effective against the parasite’s juvenile stages (schistosomula) [7]. Partly for this reason, praziquantel is not completely curative and does not prevent re-infection [8]. The reliance on a single drug for wide-scale community preventive treatment exerts a high drug pressure and could favor the emergence of praziquantel-resistant parasites. Evidence from laboratory studies suggests reduced susceptibility of schistosomes to praziquantel [9, 10]. Despite these limitations, mass administration of praziquantel has substantially reduced schistosomiasis-associated morbidity and mortality [11]. Several strategies are proposed to preserve the potency of praziquantel, including increased doses [12], repeated doses [13], or increased frequency of administration [14, 15]. The drug development pipeline for schistosomiasis is empty, and there is an urgent need to evaluate new drugs to replace or complement the use of praziquantel. In these circumstances, drug repurposing is an optimal approach to overcome the obstacles of cost and time needed to develop new drugs by exploring new indications for approved medicines currently used to treat other conditions [16]. Combination therapy is a promising strategy to improve praziquantel efficacy and delay the development of drug resistance. Possible candidates for combination therapy include praziquantel plus antimalarials such as mefloquine or artemisinin derivatives [17].

The artemisinin derivatives (artesunate, artemether, and dihydroartemisinin) are promising candidates for the treatment and chemoprophylaxis of schistosomiasis [18, 19]. This class of drugs is currently the most potent for treating malaria, for which they are used as artemisinin-based combination therapy (ACT) [20]. Artemisinin derivatives are specifically effective against the juvenile worms of the parasite [17, 19]. These differences in the mechanism of drug action support a theoretical basis for combining praziquantel with an ACT in treating schistosomiasis. The combination is likely synergistic, acting at two stages of the schistosome life cycle to cure the primary infection and block further transmission, especially in high-transmission areas. Data on the efficacy and safety of ACTs in treating schistosomiasis are scarce. However, compared to praziquantel, ACTs demonstrated significantly lower cure rates in treating children with schistosomiasis [21–24]. The results of the two studies that compared the efficacy of praziquantel plus dihydroartemisinin-piperaquine or praziquantel plus artesunate-mefloquine to praziquantel alone in the treatment of children with schistosomiasis were inconsistent [25, 26]. In one small study, praziquantel plus artesunate-mefloquine showed no benefit in the treatment of *S. haematobium*, while in a large trial, praziquantel plus dihydroartemisinin-piperaquine was associated with a substantial benefit in the treatment of *S. mansoni* [25, 26]. Hence, the additional benefit of adding an ACT to the standard praziquantel treatment for schistosomiasis remains unclear.

There is no systematic data from a single study comparing the efficacy of praziquantel plus an ACT to praziquantel alone on schistosomiasis. However, a systematic review of the available scanty evidence concluded that combining an artemisinin derivative plus praziquantel was more effective than praziquantel monotherapy [27]. WHO has approved at least five ACTs for the treatment of uncomplicated malaria: artemether-lumefantrine, artesunate plus amodiaquine, artesunate plus sulfadoxine-pyrimethamine, artesunate plus mefloquine, and dihydroartemisinin-piperaquine [20]. It is unclear which ACTs are effective and safe for treating schistosomiasis when combined with praziquantel.

## Methods

### Study objectives

The overall purpose of the SCHISTOACT study is to evaluate the role of combination therapy in treating schistosomiasis. The primary objective of the study is to evaluate the efficacy (assessed as cure rate by microscopy) and safety (frequency of adverse events) of a single dose of praziquantel combined with a 3-day course of artesunate plus sulfalene/pyrimethamine or artesunate plus amodiaquine or artesunate plus mefloquine or dihydroartemisinin-piperaquine compared with single-dose praziquantel in the treatment of children with confirmed *Schistosoma mansoni* infection.

Our secondary objectives are as follows:To assess the cumulative cure rate at 12 weeks after treatmentTo assess the egg reduction rate at 6 and 12 weeks after treatmentTo assess the re-infection rate at 12 weeks after treatment

### Study design

The SCHISTOACT study is designed as a phase III, open-label, five-arm, head-to-head, proof-of-concept, individually randomized, controlled, non-inferiority trial. The participants are randomly allocated (ratio 1:1:1:1:1) individually to one of five treatment groups. At baseline, participants in the control arm receive praziquantel (PZQ, single dose of 40 mg/kg). Those in the intervention arms receive a single dose of praziquantel (40 mg/kg) plus a 3-day course of one of four artemisinin-based combination therapies (4 mg/kg of the artemisinin component, once a day for three consecutive days, as fixed-dose WHO-recommended combination treatment for uncomplicated falciparum malaria). The four artemisinin-based combination therapies (ACTs) that are combined with praziquantel are artesunate plus sulfalene/pyrimethamine, artesunate plus amodiaquine, artesunate plus mefloquine, and dihydroartemisinin-piperaquine. These four ACTs were selected because they are widely available for malaria treatment, co-formulated, for once-daily dosing therapy, have a well-established safety profile and have all been evaluated for treating schistosomiasis with inconclusive results. The 6-week interval between the administration of study treatment and evaluation of primary endpoints has been chosen because it corresponds to the duration of schistosome larval maturation. The participants will be followed up at 6 and 12 weeks. During these follow-up visits, stool samples will be collected, and clinical assessments will be performed. All children will receive a standard dose of praziquantel at the end of the study. The study flow chart is shown in Fig. 1.

**Fig. 1 Fig1:**
[figure not shown]
Study flow chart

### Study area and population

This study population comprises primary school-age children (9–15 years) from selected primary schools in the Mwea East and Mwea West sub-counties in Kirinyaga County, central Kenya. The schools are eligible for inclusion if they have at least 50 pupils infected with *S. mansoni* detected from a screening exercise*.* The area is endemic for *S. mansoni*, with up to 75% prevalence in school children [28]. The major socio-economic activities in the study area are rice growing under irrigation and small-scale subsistence farming. Malaria transmission in the area is extremely low (< 1/1000 individuals), and elimination is envisaged.

### Sample size

The sample size is calculated using the statistical test for proportions based on the hypothesis that combination therapy using praziquantel plus an artemisinin-based combination is not inferior to praziquantel alone in treating schistosomiasis. Assuming a cure rate of 72% with praziquantel based on longitudinal studies from western Kenya [29], a cure rate of 62% (maximum difference of 10%) is considered clinically acceptable for non-inferiority of praziquantel plus an ACT combination therapy. With this non-inferiority margin, a power of 80%, and a one-sided alpha value of 0.025, a sample size of 102 children is needed in each treatment arm. To account for a 5% loss to follow-up, the total number of children to be enrolled and randomized is 540 (108 in each study arm).

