## Discussion

THE SCHISTOACT is the first clinical trial to compare the efficacy and safety of praziquantel plus four artemisinin-based combinations with praziquantel alone in treating African children with intestinal schistosomiasis. The role of artemisinin-based combination therapies in schistosomiasis control cannot be deduced from the available scanty evidence. Due to the differences in the mechanism of drug action, combination therapy using praziquantel plus an ACT has the potential to support the move from morbidity to transmission control, thus accelerating the global schistosomiasis elimination agenda. If the effectiveness and safety are confirmed, combination therapy is likely to be useful for schistosomiasis control in malaria-free settings, in patients with both malaria and schistosomiasis, as chemoprophylaxis for travelers to schistosomiasis-endemic areas, and as second-line treatment in cases of praziquantel failure. The strength of this study lies in the head-to-head comparison to contribute comprehensive evidence from a single study regarding the comparative efficacy and safety of praziquantel combined with four different artemisinin-based combination therapies in the treatment of *S. mansoni*. Overall, this study will contribute much-needed evidence to inform the global policy on the role of artemisinin-based combination therapies in schistosomiasis control.

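### The only primary hypothesis and conclusion rule for an ACT added to full-dose praziquantel is non-inferiority, which an inert ACT can meet and which does not match the stated question of added benefit

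*Protocol article*

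**What the plan says.** The protocol article, Study design, gives every arm a single 40 mg/kg dose of praziquantel. Four arms add a 3-day ACT, so nothing is replaced or reduced.

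Sample size rests on the hypothesis that "combination therapy using praziquantel plus an artemisinin-based combination is not inferior to praziquantel alone in treating schistosomiasis". Its other inputs are "Assuming a cure rate of 72% with praziquantel based on longitudinal studies from western Kenya", then "a power of 80%, and a one-sided alpha value of 0.025, a sample size of 102 children is needed in each treatment arm". The margin is set by the statement that "a cure rate of 62% (maximum difference of 10%) is considered clinically acceptable for non-inferiority of praziquantel plus an ACT combination therapy".

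Data management and analysis judges the primary hypothesis by the lower limit of the 95% confidence interval for the risk difference, set against −10. The same section plans a Pearson chi-square comparison of cure rates and counts two-sided p below 0.05 as significant for all tests. Outcomes, together with the analysis section, adds secondary comparisons with praziquantel alone on week-12 cure, egg reduction and re-infection.

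The rationale is framed differently. The Introduction says that "Combination therapy is a promising strategy to improve praziquantel efficacy" and that "the additional benefit of adding an ACT to the standard praziquantel treatment for schistosomiasis remains unclear". The Discussion says: "If the effectiveness and safety are confirmed, combination therapy is likely to be useful for schistosomiasis control in malaria-free settings".

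**The concern.** Non-inferiority usually accepts a limited loss of efficacy in return for some other advantage of a treatment that replaces the standard. Here the standard is still given in full. A lower limit above −10 therefore says one thing: the ACT does not weaken praziquantel by 10 points or more. An ACT with no effect on schistosomes has a true difference of 0 and lies inside the region that the rule calls a success.

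The Introduction asks whether the ACT adds anything. The conclusion rule cannot answer that, and the analyses that could have no conclusion attached. At stake is what a non-inferior result would be taken to mean: it could be cited in support of a longer regimen with more drugs when the data show only absence of marked antagonism.

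**Working it through.** **Inputs.** From Sample size: control cure rate 0.72, margin 0.10, one-sided alpha 0.025 (z = 1.960), power 80% (z = 0.842), 102 evaluable per arm. From Data management and analysis: a two-sided 95% interval, with the rule read as lower limit above −0.10. The variance term at 0.72 is 0.72 × 0.28 = 0.2016, and (1.960 + 0.842)² = 7.849.

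**1. The plan's own figure.** With equal true rates:

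n = 7.849 × (2 × 0.2016) / 0.10² = 316.5, so 317 per arm.

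The stated 102 does not reproduce. A figure near 102 would need something unstated, such as a true combination cure rate of about 79% (n = 100) or a margin of about 17.6 points. The dropout step does reproduce: 102 / 0.95 = 107.4, so 108, and 5 × 108 = 540. The size of 102 is a separate matter. It enters here because it fixes how often an inert ACT passes.

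**2. How often an inert ACT meets the rule (all true rates 72%).**

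- At 102 per arm: SE = √(2 × 0.2016 / 102) = 0.0629. Pass probability = Φ(0.10/0.0629 − 1.960) = Φ(−0.37) = 0.36.
- At 317 per arm: SE = 0.0357. Pass probability = Φ(2.804 − 1.960) = Φ(0.84) = 0.80.

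A simulation of 400,000 trials with four inert ACT arms sharing one control (Wald intervals) gave:

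| n per arm | one given arm passes | at least one of four | all four |
|---|---|---|---|
| 102 | 0.36 | 0.69 | 0.09 |
| 317 | 0.80 | 0.97 | 0.55 |

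Better powering makes an inert ACT pass more often. A combination that is truly 5 points worse (67%) passes about 12% of the time at 102 per arm.

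**3. What 102 per arm can show about added benefit.** For superiority at two-sided 0.05 and 80% power:

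n = 7.849 × [0.2016 + p(1 − p)] / (p − 0.72)².

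At p = 0.875 this is 7.849 × (0.2016 + 0.1094) / 0.155² = 101.6, so 102. The document gives no target benefit, so the range below is an assumption:

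| true rate, PZQ + ACT | power at 102 per arm | n per arm for 80% power |
|---|---|---|
| 77% (+5) | 13% | 1192 |
| 82% (+10) | 40% | 277 |
| 85% (+13) | 62% | 156 |
| 87% (+15) | 76% | 113 |
| 88% (+16) | 82% | 97 |

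**4. Multiplicity of a superiority step.** In the same setting of four inert arms at 102 per arm, one given lower limit exceeds 0 in 2.6% of trials. At least one of the four does so in about 8%.

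**The case against.** Several points on the other side stand.

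- A reader might infer that no test for a difference is planned and that added benefit goes unanswered. The document does not support that. It plans a two-sided chi-square test and a 95% interval on the primary cure rate, plus secondary comparisons at week 12. A lower limit above 0 would show benefit. What is absent is a superiority hypothesis, a target benefit, an order of testing and a conclusion rule.
- A reader might infer that the plan itself gives an inert ACT an 80% chance of success. Sample size never states the true difference at which power was computed. The 80% holds only at equality with about 317 per arm. At 102 per arm it is about 36%, and the authors may have assumed some benefit without saying so.
- Absence of antagonism has some value of its own. The Introduction also mentions delaying resistance, the Discussion lists patients with both malaria and schistosomiasis, and the trial is called proof-of-concept. This supports keeping non-inferiority as a step. It does not turn it into evidence of added benefit.
- The Discussion's sentence on usefulness is conditional and does not equate non-inferiority with effectiveness. Misreading is a risk, not something the document states.
- A step from non-inferiority to superiority may sit in an analysis plan that is not shown. The point does not depend on such a step being missing. The article itself fixes the hypothesis, the margin and the rule, and that stated rule does not match the stated question.

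**Conclusion.** The point holds in this form: the primary hypothesis, the sizing and the only conclusion rule are non-inferiority for an add-on to unchanged praziquantel, so success means no marked antagonism and does not address added benefit. At 102 per arm, an inert ACT meets the rule about 36% of the time per arm, and at least one of four does so in about 69% of trials. Superiority is reasonably powered only for gains of about 15 to 16 points, with about 40% power for +10.

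These figures assume a true praziquantel cure rate of 72%, 102 evaluable children in every arm, Wald or normal-approximation intervals and, for the superiority power, no multiplicity adjustment.

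**What to change.** Recruitment is complete (Trial status), so the change is one of wording, in the Abstract (Methods), Sample size, and Data management and analysis:

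1. Keep non-inferiority at −10 as step 1 and say what it shows: no antagonism of 10 points or more.
2. Add step 2: added benefit of an arm is concluded only if the lower limit of its confidence interval for the risk difference is above 0.
3. State how step 2 handles four comparisons with one control. Going from step 1 to step 2 on the same interval costs no alpha within one arm. Across four arms the unadjusted chance of at least one false superiority claim is about 8%; a Holm or Dunnett adjustment would control it.
4. State the detectable difference: about 72% versus 87.5% at 80% power, unadjusted. Any adjustment makes it larger.
5. State that non-inferiority alone will not be reported as effectiveness of the combination.

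Randomization and blinding says that the data analysts are not blinded. The change should therefore be a dated amendment made before the outcome data are analysed; otherwise step 2 should be labelled post hoc. No further data are needed. The cost is a stricter condition for claiming benefit.

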### Data management and analysis

Data collected from each participant is recorded on paper-based case report forms (CRFs) in black ballpoint pen. The principal investigator will ensure that the data in the CRFs are accurate, complete, and legible. Data from the case record forms is entered by a data clerk into computers as they accrue using the MS Access program. The data is verified by comparing it with the CRFs. Missing data is imputed as either treatment success or treatment failure (assuming the same infection intensities before and after treatment). Validated data is transferred to SPSS version 20 and STATA version 12 for statistical analyses. The CRFs and the electronic data will be kept for 5 years after the primary manuscripts are published.

Data is analyzed using SPSS for Windows version 20 (SPSS Inc., Chicago, IL) and STATA version 12.0 (StataCorp., College Station, TX, USA) packages. A two-sided *p*-value less than 0.05 is considered statistically significant for all tests.

Demographic and other baseline characteristics are compared to check for imbalances between the study groups. These measures will be tabulated from the intent-to-treat population. Significance tests are not performed to compare the differences between study groups at baseline. Where imbalances are suspected, additional analyses are performed to adjust for these variables.

To determine efficacy, both the per-protocol and intention-to-treat analyses are done, but the per-protocol analysis is the main approach. The primary efficacy outcome is the cure rate, defined as the proportion of children infected with *S. mansoni* at enrollment but not excreting eggs by week 6 after taking the study treatment. In the computation of the cure rate, children randomized to the PZQ alone study arm are considered the control group. Cure rates are compared between the treatment groups using Pearson’s chi-square test for contingency tables (in a per-protocol analysis) and summarized as absolute risk differences with 95% confidence intervals (CI). The per-protocol population is defined to include all participants who were randomized and who completed the study procedures to week 6 or 12. The primary hypothesis for non-inferiority is assessed by considering the lower limit of the 95% CI for the risk difference. Non-inferiority is concluded if the lower bound of the 95%CI from the risk difference does not exceed the non-inferiority margin of − 10.

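### The stated inputs need 317 children per arm, not 102; at 102 per arm the power for non-inferiority is about 36%, not 80%, if the true cure rates are equal

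*Protocol article*

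**What the plan says.** The Sample size section of the protocol article gives a full set of inputs:

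- Control rate: "Assuming a cure rate of 72% with praziquantel based on longitudinal studies from western Kenya".
- Margin: "a cure rate of 62% (maximum difference of 10%) is considered clinically acceptable for non-inferiority".
- Error rates and result: "With this non-inferiority margin, a power of 80%, and a one-sided alpha value of 0.025, a sample size of 102 children is needed" in each arm.

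It then allows for 5% loss to follow-up and arrives at 108 per arm and 540 in total. The Methods part of the abstract repeats the total ("A total of 540 primary school-aged children") and the margin, but no power figure.

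The decision rule under Data management and analysis matches these inputs: "Non-inferiority is concluded if the lower bound of the 95%CI from the risk difference does not exceed the non-inferiority margin of − 10". I read this as the usual rule, that the lower limit of the two-sided 95% interval must lie above −10 points. Under Outcomes, each combination arm is compared separately with praziquantel alone, and the Study design section sets equal allocation. No cure rate above 72% is assumed for the combinations anywhere in the article.

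**The concern.** A 10-point margin at a cure rate near 70% usually calls for several hundred children per arm, so 102 looks far too small. If it is, the trial lacks the power it claims for its primary efficacy hypothesis. A combination that works exactly as well as praziquantel would then more often fail the test than pass it. A reader who believes the power was 80% could take such a failure as a sign that the combination is worse, when most of it would be imprecision. The Discussion says the results should inform global policy, so that misreading would matter.

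**Working it through.** **Inputs.** Control cure rate 0.72, margin 0.10, one-sided alpha 0.025 (z = 1.960), power 80% (z = 0.842), 102 evaluable per arm, 5% loss (all from Sample size); 1:1 for each comparison (Study design). The true cure rate in the combination arms is not stated. I take it as 0.72, then vary it.

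**The plan's own figures.** The loss step reproduces: 102 / 0.95 = 107.4, rounded up to 108, and 108 × 5 = 540. The 102 does not reproduce:

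n = (1.960 + 0.842)² × 2 × 0.72 × 0.28 / 0.10² = 7.849 × 0.4032 / 0.01 = 316.5, so **317 per arm**.

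After 5% loss that is 317 / 0.95 = 333.7, so 334 per arm and 1,670 in total.

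**Other formulas that might have been used.**

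| Variant | n per arm |
|---|---|
| Non-inferiority, one-sided alpha 0.05 | 250 |
| Non-inferiority, one-sided alpha 0.10 | 182 |
| Non-inferiority, pooled variance from 62% and 72% | 338 |
| Superiority, 72% v 62%, two-sided 0.05 | 346 |
| The same, one-sided 0.05 | 273 |
| The same, two-sided 0.05, continuity-corrected | 366 |
| One-sample formulas | 125 to 177 |
| Confidence-interval precision | 77 and 155 |

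None gives 102.

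**Power at 102 per arm, 72% in both arms.**

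- Standard error = √(0.4032 / 102) = 0.0629.
- Power = Φ(0.10 / 0.0629 − 1.960) = Φ(−0.369) = **35.6%**.
- Exact binomial enumeration of the confidence-interval rule gives 36.2% with the Wald interval and 36.3% with the Newcombe interval.
- If all 108 per arm were evaluable, the normal approximation gives 37.3%.
- With a looser alpha, power at 102 is 47.8% (one-sided 0.05) or 62.1% (one-sided 0.10).

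**Precision.** The expected 95% half-width is 1.96 × 0.0629 = 0.123, or ±12.3 points. An observed difference of zero therefore gives a lower limit near −12.3, which fails. To pass, the observed difference must be about +2.3 points (12.3 − 10).

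**What would make about 102 right.** Each route changes a stated input or adds one:

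- A true combination cure rate p that solves 7.849 × [0.72 × 0.28 + p(1 − p)] / (p − 0.62)² = 102, which gives p = 0.788.
- A margin of 2.802 × 0.0629 = 0.176, or 17.6 points.
- A cure rate of about 93% in both arms (n = 103).

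| True combination cure rate (control 72%) | n per arm for 80% power | Power at 102 |
|---|---|---|
| 72% | 317 | 35.6% |
| 74% | 215 | 48.8% |
| 76% | 154 | 62.6% |
| 78% | 115 | 75.3% |
| 79% | 100 | 80.8% |

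**Across the four comparisons.** With all five arms at 72% and the shared control taken into account, all four combinations pass about 9% of the time and at least one passes about 69% of the time.

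**The case against.** The strongest reply is that the article never states the true cure rate in the combination arms. The 62% is the lowest acceptable rate, not the expected one, and equality at 72% is my assumption. The Introduction cites a large trial with a substantial benefit from one combination, and a systematic review that favours adding an artemisinin derivative. Had the investigators expected about 79%, roughly 100 per arm would be right, and a condensed article may have dropped that input.

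This is possible but not shown. The same Introduction calls the two direct combination studies inconsistent and the added benefit unclear. The sample size text ties 102 to the margin, the power and the alpha, and mentions no advantage. No whole-number rate gives exactly 102: 78% gives 115 and 79% gives 100. Even if an advantage was assumed, the sentence is wrong as printed, because the inputs it lists do not produce its result.

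Three smaller points stand:

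- The abstract carries no power figure, so nothing in it is wrong on this point.
- The 9% for all four arms is not a success criterion of the trial, since each comparison stands alone; it should be read beside the 69%.
- The analysis section reports risk differences with 95% intervals, so the imprecision will be visible, and it has no rule for declaring inferiority. That lowers the risk of misreading but does not correct the power claim.

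**Conclusion.** The concern holds. From the stated inputs the required number is 317 evaluable children per arm, about three times the 102 given. At 102 per arm, power is about 36% for each comparison (35.6% by normal approximation, 36.2% by exact enumeration), so an equally effective combination would fail about 64% of the time. These figures assume a true cure rate of 72% in both arms and make no adjustment for four comparisons. The error lies in the 102 itself. It concerns the primary efficacy hypothesis, and nothing elsewhere in the article resolves it, so it must be corrected.

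**What to change.** Trial status says recruitment ended on 30 November 2022, so the numbers stay as they are and the statement has to change. In Sample size, replace the 80% claim with text such as:

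> With 102 evaluable children per arm, power for a 10-point margin is about 36% if the true cure rate is 72% in both arms. Power is 80% only if the true combination cure rate is about 79%. The expected 95% confidence interval half-width is ±12.3 points.

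If a higher combination cure rate was in fact assumed and was documented before the data were seen, state it with its justification and keep the equal-rates figure beside it. If the abstract is to mention power, it should carry the same figures.

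Under Data management and analysis, add that a comparison whose lower limit falls below −10 while the interval includes 0 will be reported as inconclusive, not as inferior. Do not widen the margin after the fact.

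The cost is wording only. No children are added, and the stated power becomes less favourable.
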